## Abstract

Supplemental Digital Content is available in the text

## Introduction

1

Diabetes is a metabolic disease characterized by hyperglycemia. In 2018, the International Diabetes Federation (IDF) published the 8th edition of the Global Survey of Diabetes, stating that there were 114.4 million people with diabetes between the ages of 20 and 79 years in China, ranking first among all the IDF regions in 2017.^[1]^ Diabetic kidney disease (DKD) is a common microvascular complication of diabetes and is characterized by a clinical syndrome, including persistent albuminuria, elevated blood pressure, a continuous decrease in the glomerular filtration rate (GFR), and increased cardiovascular events and mortality.^[2]^ According to the UK Prospective Diabetes Study, approximately one in every 5 people would develop DKD.^[3]^ However, current statistics regarding the incidence of diabetes in China is lacking.^[4]^ In 2002, statistical data on the incidence of DKD reported that 33.6% of patients with diabetes were diagnosed with DKD in the 10 years from 1990 to 2000, with 22.5% presenting type 1 diabetes and 34.7% presenting type 2 diabetes.^[5]^ With the growing incidence of diabetes, the incidence of DKD has increased and has become the main cause of end-stage renal disease.^[6,7]^ In western medicine, DKD is treated by controlling the blood sugar, blood pressure, blood lipids, and reducing urine protein, with no effective methods to prevent the progression of DKD. Therefore, finding appropriate remedies for the prevention and treatment of DKD, as well as reducing medical costs, are important tasks for resolving this disease.

In the ancient books of traditional Chinese medicine (TCM), there is no record of the term “DKD.” Based on the clinical symptoms, etiology, and pathogenesis of DKD, the disease can be summarized as “edema,” “turbid urine” (murky urine like rice water or grease), “wasting-thirst” (any diseased state characterized by polydipsia, polyphagia, and polyuria, similar to diabetes), and “consumptive disease” (a general term for chronic deficiency diseases due to consumption of yin, yang, qi, and blood) in TCM. Practitioners of modern medicine believe that the etiology, pathogenesis, and clinical symptoms of DKD are markedly similar to those observed in nephropathy and wasting-thirst in TCM. DKD is mainly located in the spleen and kidney, providing the TCM disease name “nephropathy of wasting-thirst.”^[8]^ In the early stage, DKD is characterized by yin deficiency, and the disease is located in the liver, spleen, and kidney. During the middle stage, DKD is characterized by yang deficiency, located in the liver, spleen, and kidney. The end-stage of this disease is characterized by yin and yang deficiency, located in the spleen and kidney. With the gradual aggravation of DKD, the symptoms and syndrome elements of phlegm and blood stasis are aggravated.^[9,10]^

Currently, several experiments have confirmed that TCM prescriptions are effective in the adjuvant treatment of DKD. Zhou^[11]^ and Ai^[12]^ have shown that Qiwei granules are effective in the treatment of stages III and IV DKD with qi and yin deficiency syndrome, as well as the blood stasis syndrome. In animal experimental studies, Qiwei granules can delay the development of DKD by reducing podocyte injury and protecting renal function by upregulating the expression of nephrin^[13,14]^ and CD2AP^[15]^ in renal podocytes of DKD. Tang and colleagues^[16]^ have observed that the Huopu Xialing decoction can protect the kidney of DKD rats by inhibiting the expression of the transforming growth factor-beta 1 (TGF-β1) signaling pathway and increasing the expression of nephrin and podocin in podocytes, thus reducing podocyte apoptosis. Zhang and Yue^[17]^ have reported that the Jiangtang Baoshen decoction improves clinical outcomes in DKD patients by regulating blood lipid, blood glucose, and the urinary protein excretion rate in early type 2 DKD patients. Lu^[18]^ has documented that the Jiawei Shenling Baizhu powder granules can protect the kidneys of early DKD patients presenting spleen and kidney qi deficiency and blood stasis. Recent studies have confirmed that TGF-β1 plays an important role in the development of DKD. Liu et al^[19]^ has observed that the Compound Coptis Capsules improve the pathological changes occurring in renal function during early DKD in rats, delaying the chronic pathological progression of DKD. Here, the mechanism may be related to the regulation of the imbalance of TGF-β1/BMP-7 expression in DKD through the Smad signaling pathway. Li et al^[20]^ have documented that the Tongyu decoction combined with *Tripterygium* glycosides relieves the clinical symptoms and effectively reduces blood glucose levels. Additionally, it can regulate the levels of TGF-β1, platelet-derived growth factor-BB, and connective tissue growth factor, and improves renal function and clinical efficacy.

Liuwei Dihuang pill (LDP) has been used for over 1000 years and consists of multiple herbs, including Radix Rehmanniae (Shu dihuang), *Cornus officinalis* (Shan zhuyu), Chinese yam (Shan yao), Poria cocos (Fu ling), Alisma (Ze xie), and Cortex Moutan Radicis (Mu danpi). In China, LDP is a frequent prescription in patients with DKD. The occurrence and development of DKD is mainly mediated by inflammatory reactions, with a close relationship existing between them.^[21,22]^ Some studies have shown that one of the risk factors for the microinflammatory state observed in DKD is caused by inflammatory cytokines and adhesion molecules.^[23]^ Tan et al^[24]^ has observed that LDP can reduce the secretion of inflammatory factors, monocyte chemoattractant protein-1 and intercellular adhesion molecule, downregulating the expression of monocyte chemoattractant protein-1 and intercellular adhesion molecule mRNA, and thus delaying glomerulosclerosis. Renal interstitial fibrosis is a pathological change occurring during DKD. TGF-β1 is the core factor in promoting fibrosis, and its expression level is closely related to the occurrence of DKD.^[25]^ Furthermore, an abnormal glomerular filtration barrier caused by podocyte injury plays an important role in the occurrence and development of DKD.^[26]^ Li et al^[27]^ have reported that LDP can protect the kidneys of diabetic nephropathy rats by increasing the expression of nephrin and podocin in podocytes.

Clinical studies assessed by Feng and Li^[28]^ have noted that LDP combined with metformin can reduce postprandial blood glucose and fasting blood glucose (FBG) effectively, significantly improving the clinical symptoms in patients with type 2 diabetes. Zhao et al^[29]^ observed that the Liuwei Dihuang decoction combined with calcium dobesilate capsules reduces postprandial blood glucose, FBG, and glycosylated hemoglobin during the treatment of diabetic nephropathy; additionally, total cholesterol, triglycerides, high-density lipoprotein (HDL), and low-density lipoprotein (LDL) were improved. In the treatment of early DKD, Ma^[30]^ has shown that losartan potassium combined with LDP can improve renal function, inhibit the chronic inflammatory reaction, control blood pressure, and reduce urinary protein excretion. A study by Cui and Ma^[31]^ has demonstrated that LDP can improve the 24-hour urinary protein (24h UP) and urinary protein excretion rate. Qiu^[32]^ has reported that LDP combined with metformin hydrochloride sustained-release tablets reduces the incidence of adverse reactions in patients with DKD. These clinical studies have confirmed that LDP can treat DKD, but the quality of these studies is inadequate.

To date, high-quality, evidence-based medicine confirming the clinical efficacy and safety of LDP in DKD treatment remains scarce. Therefore, we designed a randomized controlled trial to evaluate the efficacy and safety of LDP in the adjuvant treatment of DKD.

## Methods and design

2

### Objectives

2.1

This randomized controlled trial is aimed to evaluate the efficacy and safety of LDP in the adjuvant treatment of DKD.

### Design

2.2

The proposed study is a prospective, double-blind, randomized, placebo-controlled clinical trial to evaluate the efficacy and safety of LDP compared with a placebo. The clinical trial number is ChiCTR2000029800, which has been registered in the Chinese Clinical Trial Registry (http://www.chictr.org.cn/showproj.aspx?proj=10862) on February 14, 2020. A 2-week run-in period will be initiated after obtaining the written informed consent. Next, 124 eligible participants will be randomly allocated to either the LDP group or the control group in a 1:1 ratio. After allocation, patients in the experimental group will receive basic treatment and LDP, while patients in the control group will be treated with the basic treatments and placebo. Both groups will undergo a 24-week treatment, with follow-ups at 0, 4, 8, 12, 16, 20, and 24 weeks. In this study, we aim to observe the efficacy and safety of LDP when compared with western medicine alone for DKD treatment. The Standard Protocol Items: Recommendations for Interventional Trials (SPIRIT) 2013 statement will be followed by this trial protocol (see Supplemental Digital Content: Additional file 1 and Fig. 1 for the schedule of enrollment, interventions, and assessments).^[33]^ The study flow chart is shown in Figure 2.

**Figure 1 F1:**
[figure not shown]
The schedule of enrollment, interventions, and assessments. BUN = blood urea nitrogen, ECG = electrocardiogram, eGFR = estimated glomerular filtration rate, FBG = fasting blood glucose, HbA1c = glycosylated hemoglobin, HDL-C = high-density lipoprotein cholesterol, 2hPG = postprandial 2-hour blood glucose, LDL-C = low-density lipoprotein cholesterol, LDP = Liuwei Dihuang pills, SCr = serum creatinine, TC = total cholesterol, TCM = traditional Chinese medicine, TG = triglyceride, UA = uric acid, UAER = urinary albumin excretion rate. ^∗^Laboratory tests include routine blood test, routine stool test, liver function test, and C-reactive protein.

**Figure 2 F2:**
[figure not shown]
The flow chart of study design. DKD = diabetic kidney disease, LDP = Liuwei Dihuang pills.

### Ethics approval

2.3

This study will be performed in accordance with the regulations of the Declaration of Helsinki (Edinburgh 2013 version) established by the World Medical Congress. The final amendments (version: 2.0) and the consent forms were reviewed and approved by the China Ethics Committee of Registering Clinical Trials (approval no: ChiECRCT20200028). If any amendment is made to the protocol, further approval must be obtained from the Ethics Committee.

### Recruitment

2.4

A total of 124 participants will be recruited at the endocrine clinics of the Hospital of Chengdu University of Traditional Chinese Medicine (Chengdu, China). The recruitment will be carried out through local advertisements and doctor referrals, posters, and the Internet. The patients were included after the endocrinologist diagnoses according to the inclusion and exclusion criteria of the study. Before enrollment, participants will be provided with detailed information about the clinical study, including purpose, process, schedule, and possible risks, and benefits. All patients need to sign an informed consent form before any medical assessment.

### Sample size

2.5

The sample size will be calculated based on the primary outcome (24h UP). According to a previous study,^[34]^ the average 24h UP level of the control group is 100.6 mg/24 h, with a standard deviation of 23 mg/24 h. After LDP treatment, the average 24 h UP level in the experimental group was 89 mg/24 h, with a standard deviation of 12 mg/24 h. The following formula is employed to calculate the sample size that allows obtaining a significantly lower 24h UP in the experimental group after 24 weeks of treatment: 

where *σ*^2^ is the overall variance, estimated as the sample variance *s*^2^: 

The proportion of participants between the experimental and control groups is set to 1:1 (*k* = 1). The study is designed to have a power of approximately 90% and a 2-sided significance level of 0.05 (*a* = 0.05, *β* = 0.1). *μ*_2_, *μ*_1_, *s*_1_, and *s*_2_ are the mean and standard deviations in the control and experimental groups, respectively. This resulted in *n* = (1.96 + 1.28)^2^ × (23^2^ + 12^2^)/(100.6–89)^2^ ≈ 56. Thus, after assuming a dropout rate of 10%, the sample size for patients with DKD in each group was determined as 62, and the total sample size is 124.

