### Outcome measures

3.2

Primary outcome: The primary outcome is determined as the change in 24h UP, from the baseline to the end of the treatment phase (week 24).

Secondary outcomes:

1.Changes in SCr and eGFR: eGFR will be used to assess the kidney function of participants with CKD-EPI creatinine equation of 2009^[37]^ (at weeks 4, 8, 12, 16, 20, 24).2.Change in the urinary albumin excretion rate from baseline to week 24 (at weeks 4, 8, 12, 16, 20, 24).3.Improvement of TCM syndromes and symptoms from baseline to week 24 (at weeks 4, 8, 12, 16, 20, 24).4.Changes in FBG and postprandial 2-hour blood glucose (2h PG) from baseline to week 24 (at weeks 4, 8, 12, 16, 20, 24).5.Changes in blood lipids from baseline to week 12 and week 24, including total cholesterol, triglyceride, HDL cholesterol, and LDL cholesterol (at weeks 4, 8, 12, 16, 20, 24).

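### The stated 90% power is for the level of 24h UP, but the primary outcome is its change from baseline, so the power for that outcome is unknown and may be lower or higher.

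*Protocol article*

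**What the plan says.** Section 2.5 bases the sample size on the primary outcome and takes its inputs from one earlier study. For the control group, "the average 24h UP level of the control group is 100.6 mg/24 h, with a standard deviation of 23 mg/24 h". After LDP treatment, the "level in the experimental group was 89 mg/24 h, with a standard deviation of 12 mg/24 h". The aim is "obtaining a significantly lower 24h UP in the experimental group after 24 weeks of treatment". These are levels, and the formula uses their two variances and nothing else. On power, the section states: "The study is designed to have a power of approximately 90% and a 2-sided significance level of 0.05". It gives 56 per group, raised to 62 for 10% dropout, 124 in total.

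Section 3.2 defines a different quantity: "The primary outcome is determined as the change in 24h UP, from the baseline to the end of the treatment phase (week 24").

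Section 3.7 lists group *t* tests or nonparametric tests for measurement data. It mentions no adjustment for the baseline value and assigns no specific model to the primary outcome.

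**The concern.** Under randomisation the expected between-group difference in change equals the expected difference in week-24 level, so the 11.6 mg can serve for either. The variance cannot. The variance of a change depends on the baseline SD and on the correlation between the baseline and week-24 values, and the article gives neither.

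The SD of 12 after LDP helps to keep the calculated sample small. Randomised arms come from one baseline distribution, so a small SD after treatment in one arm does not give that arm an equally small SD of change.

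The 90% is the only justification given for 124 patients. If it is carried forward as the power for the primary outcome, a non-significant result may be presented as coming from a 90%-powered comparison when the power for that comparison was never worked out.

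**Working it through.** **Inputs from section 2.5:** means 100.6 and 89, so the difference is 11.6; SDs 23 and 12; two-sided 0.05; power 90%; 1:1 allocation; 56 per arm before dropout.

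**Step 1. The plan's own figure.** n = (1.96 + 1.28)² × (23² + 12²) / 11.6² = 10.4976 × 673 / 134.56 = 52.5, so 53 per group. The article prints 56. The discrepancy is on the safe side, and the steps below use 56.

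**Step 2. Power for the level at 56 per arm.** The standard error is √(673/56) = 3.467 and 11.6/3.467 = 3.35. The Welch noncentral *t* gives 91.1%. The statement of about 90% is therefore right for the level.

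**Step 3. Variance of the change.** In each arm, Var(change) = s0² + s1² − 2·r·s0·s1, where s0 is the baseline SD, s1 the week-24 SD (23 or 12) and r the correlation.

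Assumptions, none of them given in the article: s0 and r are the same in both arms; the printed SDs are taken as week-24 SDs; s0 lies between 12 and 23, the two printed SDs.

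Worked case, s0 = 23 and r = 0.5:
- Control: 529 + 529 − 529 = 529 (SD 23.0).
- LDP: 529 + 144 − 276 = 397 (SD 19.9).
- Standard error √(926/56) = 4.07; 11.6/4.07 = 2.85; power 81%.

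Other correlations at s0 = 23:

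| r | Power for change, 56 per arm |
|---|---|
| 0 | 54% |
| 0.3 | 68% |
| 0.5 | 81% |
| 0.7 | 94% |

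**Step 4. Correlation needed for 90% power, 56 per arm.**

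| Common baseline SD (assumed) | r needed |
|---|---|
| 12 | 0.31 |
| 15 | 0.40 |
| 18.34 (root mean square of 23 and 12) | 0.50 |
| 23 | 0.64 |

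**Step 5. Check by algebra.** The two change variances sum to 2·s0² + 673 − 2·r·s0·(23 + 12). This equals the 673 used for the level when r = s0/35, that is 0.34 at s0 = 12 and 0.66 at s0 = 23. Below that correlation the change is noisier than the level; above it the change is less noisy. The values agree with Step 4, allowing for the start at 91.1% rather than 90%.

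**Step 6. Baseline-adjusted week-24 level.** With residual variance s1²(1 − r²) in each arm, power at 56 per arm is 91% at r = 0, 93% at r = 0.3 and 97% at r = 0.5. Apart from the degree of freedom spent on the covariate, it does not fall below the level calculation for any r, provided the SDs of 23 and 12 are right.

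**The case against.** The strongest reply is that the direction is open. The expected difference is the same for level and change, and at a high enough correlation the change score has more than 90% power. A reader might infer from the lower rows that the design never had 90% power. The documents do not support that: they give no correlation and no baseline SD, and 94% at r = 0.7 is as consistent with them as 68% at r = 0.3.

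A baseline SD of 23 is also the less favourable of the two printed SDs. At 12 the required correlation halves to about 0.31. This stands, and it is why the result is given as a range.

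Section 3.7 plans intention-to-treat with last observation carried forward, so up to 62 per arm may be analysed. With 62 and a baseline SD of 23, the required correlation falls from 0.64 to 0.59, and power at r = 0.5 rises from 81% to 85%. That narrows the gap without closing it, and it leaves aside any dilution of the effect by carried-forward values.

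Section 3.7 lists tests by data type, and the exact primary model may stand in an analysis plan that is not shown. That is fair, but section 2.5 does state a calculation for the primary outcome, and it is for a different quantity from the one defined in section 3.2.

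A reader might also infer that the trial admits patients with any 24h UP, so that the planning SDs are too small. The listed eligibility criteria give no such limit, but they require DKD by the 2014 consensus. Those diagnostic criteria are in Table 1, which is not shown and may contain a urinary criterion. The article gives no other SD either, so this reading is not pursued.

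**Conclusion.** The point holds as a mismatch: the power in section 2.5 is for the level of 24h UP, the outcome in section 3.2 is the change, and nothing in the article links the two. The true power for an unadjusted comparison of change may be below or above 90%. With 56 per arm and 11.6 mg, it reaches 90% only if the baseline-to-week-24 correlation is at least about 0.31 (baseline SD 12) to 0.64 (baseline SD 23).

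This rests on the assumed baseline SDs, a correlation common to both arms, and reading both printed SDs as week-24 values. The article does not give the time point of the control figure explicitly.

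It should be fixed, but it does not undermine the design. The sample size need not change, and a baseline-adjusted analysis resolves the mismatch if the planning SDs hold.

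**What to change.** Preferred: state in section 3.7 that the primary analysis is an analysis of covariance of week-24 24h UP with the baseline value as covariate, and word sections 2.5 and 3.2 to match. With baseline as covariate, analysing the week-24 value or the change gives the same treatment estimate, so the clinical question is unchanged. Section 2.5 can then keep its calculation, described as a conservative bound if the SDs of 23 and 12 hold.

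Alternative: keep the unadjusted change score. Section 2.5 should then give the assumed SD of change, or the baseline SD and correlation, with their source. It should also give the resulting power at 124 patients and a short table of power against correlation and baseline SD in place of the single 90%.

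Cost: a few sentences, and for the preferred route one named model fixed before unblinding. No extra patients or visits are needed. Under the alternative, the stated power may turn out less favourable than 90%.

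### The printed sample-size expression equals 52.5, so 53 per group, and not the stated 56

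*Protocol article*

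**What the plan says.** Protocol article, section 2.5 (Sample size), bases the calculation on 24-hour urinary protein, with figures taken from one earlier study. For control, "the average 24h UP level of the control group is 100.6 mg/24 h, with a standard deviation of 23 mg/24 h"; after treatment, the mean "in the experimental group was 89 mg/24 h, with a standard deviation of 12 mg/24 h". The design values are a "2-sided significance level of 0.05" and a "power of approximately 90" per cent, with equal allocation.

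The numbers are then put into the normal-approximation formula for two means, and the result is given as "1.96 + 1.28)^2^ × (23^2^ + 12^2^)/(100.6–89)^2^ ≈ 56". The last step reads "after assuming a dropout rate of 10%, the sample size for patients with DKD in each group was determined as 62", which gives 124 in total. The same 124 appears in section 2.2 (Design), section 2.4 (Recruitment) and section 2.6 (Randomization and allocation concealment).

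**The concern.** The article gives the full expression and its value, so any reader can check it, and the two sides do not agree. The two general formulas in this section were lost when the text was read from PDF, but the line with the numbers is intact, so nothing has to be guessed.

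This calculation is the only justification given for the enrolment target. A result that cannot be reproduced leaves open whether the arithmetic slipped or an input was printed wrongly. In the first case the target has a small surplus. In the second the surplus disappears, and anyone who later compares the observed standard deviations or difference with the plan would be using the wrong values.

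**Working it through.** **Inputs, all from section 2.5.** z for two-sided α of 0.05 = 1.96; z for β of 0.1 = 1.28; control mean 100.6 and SD 23; experimental mean 89 and SD 12 (mg/24 h); 1:1 allocation; dropout 10%.

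**Step 1: the printed expression.** n = (z_α/2 + z_β)² × (s₁² + s₂²) / (μ₂ − μ₁)²

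- (1.96 + 1.28)² = 3.24² = 10.4976
- 23² + 12² = 529 + 144 = 673
- (100.6 − 89)² = 11.6² = 134.56
- n = 10.4976 × 673 / 134.56 = 7064.88 / 134.56 = **52.5, so 53 per group**

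Unrounded z values give 52.55, also 53. The stated 56 is not reproduced.

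**Step 2: other methods on the same printed inputs.**

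| Variant | n per group |
|---|---|
| One-sided α | 43 |
| Noncentral t, pooled or Welch | 54 |
| Small-sample t correction added to 52.5 | 53.5 to 54.4 |
| Rank-test efficiency (52.5 or 53 divided by 0.955) | 55.0 to 55.5 |
| 80% power | 39.2 |
| 95% power | 65.0 |

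The rank-test allowance comes closest; its upper value would round up to 56. But the article prints the plain normal formula and mentions no such allowance, so it cannot make the printed equality true.

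**Step 3: dropout.**

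- From 53: 53/0.9 = 58.9, so 59 per group and 118 in total.
- From 56: 56/0.9 = 62.2 and 56 × 1.1 = 61.6. Both give 62 to the nearest whole number; only strict rounding up of 62.2 gives 63.

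**Step 4: power on the printed inputs** (difference 11.6, s₁² + s₂² = 673, two-sided 0.05, pooled noncentral t).

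| n per group analysed | Power |
|---|---|
| 53 | 89.7% |
| 54 | 90.3% |
| 55 | 90.8% |
| 56 | 91.3% |
| 62 | 93.7% |

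The normal approximation gives 90.2% at 53, 91.7% at 56 and 94.1% at 62. With 10% loss, 62 × 0.9 = 55.8, so the rows for 55 and 56 apply.

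**Step 5: could an input, rather than the result, be wrong?** These are illustrations only; the article does not say that any of them occurred.

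- Control SD 24 instead of 23: 10.4976 × (576 + 144) / 134.56 = 56.2.
- Experimental mean 89.4, printed as 89 (difference 11.2): 7064.88 / 125.44 = 56.3.
- Experimental mean 89.3, printed as 89 (difference 11.3): 7064.88 / 127.69 = 55.3, which rounds up to 56.

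In the first two cases, 55 to 56 patients per group give about 88.7% to 89.4% power by noncentral t.

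**The case against.** The strongest objection is that nothing depends on the slip. On the printed inputs 124 is more than enough, power with 10% loss is about 91%, and no design element changes. This stands, and it limits the point to a correction of the text. The analysis in section 3.7 supports it further: it follows intention to treat with the last observation carried forward, so the number analysed could approach 62 per group, where power is 93.7%.

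A second objection is that 56 may come from unrounded inputs. The control mean is printed to one decimal and the other three values to none, and an experimental mean of 89.3 or 89.4 would yield 56. This also stands as a possibility. It does not make the printed equation right, but it is a reason to check the inputs before replacing 56 with 53.

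Two stronger readings are tempting. A reader might infer that the dropout step is also wrong and that 56 should have become 63. The article gives neither a dropout formula nor a rounding rule, and 62 follows from 61.6 or from 62.2 rounded to nearest, so the text does not support this. A reader might also infer that the trial is underpowered. On the stated inputs the opposite is true. Nor is the lack of a t correction a fault: the normal formula is a standard choice, and the correction adds one patient per group.

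**Conclusion.** The point holds in narrow form. The printed expression equals 52.5, so 53 per group, and the stated 56 is 3 patients per group too high on its own inputs. That evaluation is certain, because every number in it is printed.

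The consequence is small. If the printed means and SDs are right, the plan exceeds its need by 124 − 118 = 6 patients, or by 4 if the t-based 54 is used (54/0.9 = 60 per group, 120 in total). If an input was rounded or misprinted as in the illustrations, the surplus goes and power with 10% loss is about 89%. The article alone cannot settle which case applies. This verdict takes the planning difference and SDs as given; whether they suit this population is a separate question.

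**What to change.** First check the two means and two SDs in section 2.5 against the cited study and the original calculation.

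- **If they are confirmed:** restate the result as 52.5, so 53 per group, and 59 per group (118 in total) after dividing by 0.9. Keep 62 per group (124) as a rounded-up target, and give its power as about 91% with 10% loss.
- **If an input was rounded or misprinted:** print the correct value, show that the expression then gives 56, and restate the power for 62 per group with 10% loss.

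In either case, one clause naming the dropout formula and the rounding rule would let a reader reproduce the final step; this is tidying only. The cost is one look-up and a text correction. Enrolment and the 124 random numbers stay as they are.
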